### Relevant concomitant care permitted or prohibited during the trial {11d}

Participants cannot participate in interdisciplinary pain rehabilitation programs during the tapering period. Unimodal treatment as in usual care is however permitted.

### Provisions for post-trial care {30}

All participants are covered by the national health insurance system in the event of suffering harm during the trial.

### Outcomes {12}

Outcome measurements are chosen in regard to recommendations for clinical trials in a chronic non-cancer pain population [31]. Primary outcomes are chosen as evaluation of methods on tapering trials in line with recommendations [28].

#### Primary outcomes

Consumption of opioids, measured as MME, will be evaluated using data extracted from the Swedish drug register of the National Board of Health and Welfare (SDPR) where registration of all withdrawals of prescribed drugs is made. MME will be calculated using these data. At all baseline visits and 12-month follow-ups, the MME will be calculated for the preceding 90 days, but at 4 months after the intervention, the dose will be calculated for the preceding 30 days as the intervention is estimated to last approximately 3 months.

Self-reported opioid consumption will also be evaluated and reported in MME. Calculation of morphine equivalent dose will be performed with conversion factors used in Cochrane review [7].

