### Trial design {8}

The design of the present study is an RCT, which is under recruitment and conducted among patients with long-term pain who have been accepted to undergo a structured intervention aiming to taper opioid long-term treatments. The study population will be randomly allocated to either (1) the start of tapering opioids immediately or (2) the control group who will return to usual care and commence tapering of opioids 4 months later. A 12-month follow-up after the start of the intervention is included (Fig. 1). The study lies within a superiority framework. Primary endpoints are hypothesized to generate a decrease in opioid use in comparison to controls.

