### Intervention description {11a}

After randomization and at the baseline visit, a written individual treatment plan is established by the physician and reviewed by the nurse and participant in concordance with guidelines [27, 30].

The written treatment plan includes the following:
Information on well-known risks and side effects of long-term opioid treatments of long-term pain.Possible symptoms of withdrawal that might appear during tapering.The participant’s daily intake of opioid converted to milligram morphine equivalent dose per day (MME).The participants’ individual goals with tapering opioids.Information about follow-up: weekly follow-up at the commencement of tapering. Nurses’ follow-up is then performed according to participants’ needs which can be weekly or less frequent.The architecture of the tapering process where the participant is advised to decrease the dosage with approximately 5–10% from starting dose every week.The rationale for switching to a single preparation of extended-release opioid preparation if immediate-release opioids are used. If more than one type of opioid is used, tapering is performed with one drug at the time. If the patient is willing to taper pregabalin or benzodiazepines, this may be performed as well.Participant’s approval to prescribing doctor during the trial to use the Swedish drug register of the National Board of Health and Welfare. Opioids are prescribed with 7–30-day intervals or may be delivered by multi-dose dispensing by staff in intervals of 1 or 2 weeks if there are problems in following prescriptions.Information about urine drug screening and blood test for B-PEth that may occur at any time during the trial and should be performed on demand within 48 h. Refusal to perform the test is equal to a positive test. Results on drug screening are delivered approximately 1 week after sampling and are sent by post. If drug screening at baseline is without remark, no more drug screening is performed during tapering.Consequences that may occur if the treatment plan is not followed.The collaborative decision physician–participant on however evidence-based and safe pharmacological treatments for long-term pain, i.e., serotonin–norepinephrine reuptake inhibitor (SNRI), amitriptyline, and gabapentin, is in question to be tested after or during tapering.During tapering, rescue medication may be used. NSAID used for increased pain is and alimemazine, mirtazapine, or equal drug is in question to use for sleeping disturbance.Named contact nurse during the trial.

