## Statistical methods

### Statistical methods for primary and secondary outcomes {20a}

All statistical analyses will be performed with the SPSS software (version 25, IBM Inc). Continuous data will be expressed by means, standard deviation and 95% confidence interval, and categorical data in numbers and percentages.

The intervention arm (tapering opioids) will be compared with control (waiting list) for primary and secondary outcomes at 4 months of follow-up. Statistical analysis of differences between groups will be performed per protocol (attending follow-up 4 months after the start of the intervention and attending second baseline visit in controls) with a paired *t*-test regarding the primary outcome and a Wilcoxon signed-rank test regarding secondary outcomes.

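### At the 4-month comparison the register dose is averaged over 30 days in the intervention arm but, on the natural reading, over 90 days in controls

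*Protocol article*

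**What the plan says.** All references are to the protocol article.

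- **Window at baseline and 12 months** (Outcomes {12}, Primary outcomes): "At all baseline visits and 12-month follow-ups, the MME will be calculated for the preceding 90 days".
- **Window at 4 months** (same section): "at 4 months after the intervention, the dose will be calculated for the preceding 30 days as the intervention is estimated to last approximately 3" (the last figure is in months).
- **Comparison** (Statistical methods {20a}): the intervention arm "will be compared with control (waiting list) for primary and secondary outcomes at 4 months of follow-up". The analysis set is those "attending follow-up 4 months after the start of the intervention and attending second baseline visit in controls".
- **What controls have received by then** (Trial design {8}): they are "the control group who will return to usual care and commence tapering of opioids 4 months later", so at month 4 they have had no intervention.
- **Retention** (Methods for additional analyses {20b}): percentage change is taken from the post-intervention follow-up, which is month 4 in the intervention arm and month 8 in controls.
- **Supply length under the treatment plan** (Intervention description {11a}): "Opioids are prescribed with 7–30-day intervals".

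**The concern.** The window rule follows the type of visit, and at month 4 the two arms are at different types of visit. A tapered patient is at the 4-month follow-up and gets 30 days. A control is at a baseline visit, the second one, and gets 90 days. The stated reason for the shorter window is that the taper lasts about 3 months, which concerns tapered patients only. Nothing in the article gives controls a 30-day window at month 4.

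The primary endpoint would then be measured by a rule that depends on allocation. A mean over a longer look-back sits closer to where the dose was earlier. If controls are drifting, their month-4 value lags behind their actual month-4 dose, and the tapered arm's value lags less. The lag enters the treatment difference directly.

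Some control decline is plausible. Eligibility requires that the participant or the prescriber is asking for a taper. Before randomisation everyone is told about opioid harms, and tapering is urged for those above 100 mg or taking benzodiazepines as well. The article does not quantify any such decline.

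**Working it through.** **1. The plan's own figure.** With d = 0.5, 80% power and two-sided α = 0.05 (sidedness is not stated, but the two-sided calculation matches), n = 2(1.960 + 0.842)²/0.5² = 62.8, so 63 per arm. Then 63/0.9 = 70. The stated 70 per group reproduces, and the window length does not enter it.

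**2. Which days are averaged.** With the month-4 visit at day 120, a 30-day window covers about days 90–120 (midpoint 105) and a 90-day window about days 30–120 (midpoint 75). For a linear dose path the window mean equals the dose at the midpoint. The two windows therefore differ by exactly 30 days of drift.

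**3. Effect on the control value.** Let the control dose be 100 at day 0 and change linearly by c points over 120 days. The values of c are assumptions.

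- 30-day mean = 100 + c × 105/120 = 100 + 0.875c
- 90-day mean = 100 + c × 75/120 = 100 + 0.625c
- 90-day minus 30-day = −0.25c

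| Control drift over 120 days | 30-day mean | 90-day mean | Overstatement of control dose |
|---|---|---|---|
| 0% | 100 | 100 | 0 |
| −10% | 91.25 | 93.75 | 2.5 |
| −20% | 82.5 | 87.5 | 5.0 |
| −30% | 73.75 | 81.25 | 7.5 |
| +10% | 108.75 | 106.25 | −2.5 |

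The last column, in points of starting dose, is also the shift in the between-arm difference. A positive value favours the intervention.

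**4. Noise.** Take a constant dose, regular supplies of P days, a random start, and the dispensed amount divided by the window length W. None of these is fixed by the article. The SD as a percentage of the true dose is 100(P/W)√[f(1 − f)], where f is the fractional part of W/P.

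- 14-day supplies: 46.7 × 0.350 = 16 with W = 30; 15.6 × 0.495 = 7.7 with W = 90.
- 30-day supplies: f = 0, so 0 with either window if supplies are perfectly regular.
- 60-day supplies (assumed): 200 × 0.5 = 100 with W = 30; 66.7 × 0.5 = 33 with W = 90.

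On the natural reading, the 30-day window falls on tapered patients with supplies of 7 to 30 days, and the 90-day window on controls whose supply length is not stated. With 14-day supplies in the tapered arm the SD is 16. In controls it is 0 with 30-day and 33 with 60-day supplies. Noise may differ by arm, but which arm is noisier cannot be said.

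**5. Retention analysis.** The post-intervention dose at month 4 or 8 uses 30 days and the 12-month dose uses 90. By step 2, the 12-month value again looks 30 days further back than a matching window would. In both arms, part of any measured change or stability over that interval is due to the window.

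**The case against.** The strongest reply is that the article does not state the controls' window at month 4 in so many words. The second baseline visit is named only in the parenthesis that defines the per-protocol set. The abstract lists common time points, the comparison is described as being at 4 months, and the reference to all baseline visits could mean every participant's single baseline. This stands as a reason for caution about intent. It does not remove the problem: the text has two kinds of visit and two windows, calls the controls' month-4 visit a baseline, and places their post-intervention follow-up at month 8. If a common 30-day window was intended, the article does not say so.

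Two further points stand. The 30-day window is sensible for tapered patients, because 90 days would average in the taper itself. Self-reported consumption is also listed under primary outcomes and does not depend on the register window.

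A reader might infer much larger effects, which the article does not support:

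- **A 21-point artefact.** A patient tapering by 5% of starting dose per week shows 1 − 0.05 × 105/7 = 25% remaining on 30 days and 1 − 0.05 × 75/7 = 46% on 90 days. This puts both windows on one tapering patient. It would be a between-arm bias only if controls tapered at the intervention's rate, and they have not started.
- **Many false responders.** With 60-day supplies, half of stable patients would have no dispensing in a 30-day window. That pairs the short window with a supply length that the treatment plan does not give the tapered arm.
- **A flawed sample size.** The calculation uses only a standardised effect, so it contains no variance that could be said to omit dispensing noise.
- **A raw pack count.** The article does not say how dispensings become a daily dose. That detail may properly sit in the analysis plan.

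**Conclusion.** The concern holds: on the natural reading, the primary outcome is averaged over different windows in the two arms at the one randomised comparison. The expected bias is zero if control doses are stable. For assumed linear control declines of 10 to 30% over 120 days it is about 2.5 to 7.5 points of starting dose in favour of the intervention, and it reverses if control doses rise. Size and sign rest on a control trend that the article does not give, so no fixed direction can be claimed.

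The likely effect is modest beside the 50% reduction that defines a responder. It should still be corrected, because it is an allocation-dependent measurement rule on the primary endpoint. It should be settled before the register data are extracted, since neither outcome assessment nor analysis is blinded.

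**What to change.** - **Randomised comparison:** calculate register MME over the same calendar window in both arms, counted from randomisation and not from the attended visit, for example days 91–120.
- **Sensitivity analysis:** repeat the comparison with a 90-day window in both arms.
- **Controls' pre-taper baseline:** keep the 90-day value at the second baseline visit for this purpose only.
- **Retention analysis:** use one window length for the month 4 or 8 dose and the 12-month dose, at least as a sensitivity analysis.

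The cost is small. The register extract is taken after all follow-ups close, so no new data, visits or participants are needed, and the 70 per group is unaffected. The downside is that a shared 30-day window is noisier for any control with long supply intervals (SD 100% against 33% of true dose with assumed 60-day supplies). The 90-day sensitivity analysis addresses this.

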#### Secondary outcomes

Secondary outcomes are effects on pain, pain cognitions, mental health, life quality, and physical and psychological functioning using validated questionnaires registered in SQRP [32]. Pain rating will be evaluated using NPRS. Pain cognitions are mapped with the Tampa Scale of Kinesiophobia (TSK), Pain Catastrophizing Scale (PCS), and Chronic Pain Acceptance Questionnaire (CPAQ-8). Hospital Anxiety and Depression is applied to assess mental health, and RAND-36 will be used to assess the quality of life and functioning entailing physical, mental, and general health.

##### Numeric Pain Rating Scale (NPRS)

NPRS was used to capture the patient’s level of pain intensity. Patients rate their average level of pain during the last week. The 11-point scale spans from the left with the phrase “no pain,” i.e., 0, and on the right to the phrase “worst imaginable pain,” i.e., 10. Numeric pain scales have been shown to be reliable and valid [33–35].

##### Pain in anatomical regions

Participants report pain besides intensity also from different anatomical regions in the body including the head, joint, and soft tissue. There are 36 sites optional for the report. The number of pain sites will be analyzed.

##### Tampa Scale of Kinesiophobia (TSK)

The fear-avoidance model applied on long-term pain led up to the introduction of the term “kinesiophobia” and the development of TSK [36, 37]. Kinesiophobia was defined as “a condition in which a patient has an excessive, irrational and debilitating fear of physical movement and activity resulting from a feeling of vulnerability to painful injury or re-injury.” TSK has been found to strongly predict levels of pain intensity and disability in patients with musculoskeletal pain [38].

The TSK employs a 4-point Likert scale, with scoring options ranging from 1 (strongly disagree) to 4 (strongly agree), and encompasses 17 items related to pain, fear of movement, and re-injury. The total score of the original 17-item version ranges between 17 and 68, with a higher score indicating a higher degree of kinesiophobia. The Swedish version has been tested and validated [39–41].

##### Pain Catastrophizing Scale (PCS)

The PCS comprises 13 items that are rated from 0 to 4 with the endpoints 0 (“Never”) to 4 (“All the time”) and was constructed to assess pain-related catastrophizing [42]. Catastrophizing includes three factors: (a) Helplessness, i.e., perceived helplessness in situations when pain is present (six items); (b) Rumination, concerning vigilance toward the pain experience (four items); and (c) Magnification, i.e., the tendency to magnify the threat value of pain (three items). The Swedish version has recently been validated with psychometric properties supporting internal consistency (Cronbach’s *α* 0.92) and structural validity as well as indicating support for the three-factor solution [43].

##### Chronic Pain Acceptance Questionnaire (CPAQ-8)

Pain acceptance measures two main classes of behaviors represented by respective subscales: Activity Engagement (“AE,” score range 0–24) and Pain Willingness (“PW,” inverted score range 0–24). The items are rated from 0 (never true) to 6 (always true) and higher values indicate higher acceptance to long-term pain. CPAQ-8 scales exhibit good internal consistency (alpha ≥ 0.80), correlate significantly with related constructs, and have also been tested for validity in people living with long-term pain [44, 45].

##### Hospital Anxiety and Depression Scale (HADS)

HADS was constructed for patients in medical settings [46]. It entails 14-item measures of anxiety (7 items) and depression (7 items) symptoms over the course of a week. Items are rated on a 4-point scale (0 = not all; 3 = very often) and the anxiety and depression subscales range from 0 to 21. Higher scores indicate greater severity. The cutoff points for anxiety and depression are 0–7 for non-cases, 8–10 for doubtful cases, and 11–21 for cases. The Swedish version applied in this study has exhibited excellent internal consistency for the total (*α* = 0.90), anxiety (*α* = 0.84), and depression scales (*α* = 0.82) and has correlated significantly with other measures of anxiety and depression consistent with the English original [47].

##### RAND-36

The non-profit organization RAND Corporation USA, promoting Medical Outcomes Study, originally developed SF-36. The Swedish RAND-36 is a modern translation of SF-36. Recent psychometric evaluation of the Swedish version gave support for the reliability and responsiveness [48]. RAND-36 reflects current perceptions of health. Subjects are asked questions related to how well they have been coping during the last 4 weeks.

RAND-36 encompasses questions from eight domains (subscales), i.e., physical functioning, role physical, bodily pain, general health, vitality, social functioning, role emotional, and mental health. The scores are subsequently transformed in a standardized way into a 0–100 scale where higher scores indicate better health. Minor differences exist between RAND-36 and SF-36 in scoring procedures for bodily pain and general health of the eight subscales. The RAND-36 does not have an authorized algorithm for calculating Mental and Physical Component Summary scores.

##### Use of health care

Reports of the utilization of health care due to long-term pain during the last 12 months are collected. “How many times have you sought medical assistance by a physician due to your pain in the last twelve months” with the following options: 0–1, 2–3, or more than 4 times. Patients reporting more than four visits in the last 12 months tend to have a multitude of visits [49, 50].

##### Baseline characteristics

Characteristics including age, gender, length, weight, country of birth, education, and employment/sickness compensation are included in baseline questionnaires.

#### Additional data collection

##### Presence of substance use disorder (SUD)

A non-validated structured interview is performed based on DSM-5 criteria for SUD and information about the clinical evaluation for the presence of SUD [29]. Information regarding the presence of SUD in the family is also collected in this interview.

##### Drug screening

Analysis of prescribed and illicit drugs is performed in the first line by enzyme-immune analysis.

If the test results indicate the use of a drug that is not prescribed, a mass spectrometry method is used.

##### Opioid-induced symptoms

A non-validated instrument for the measurement of self-reported symptoms during opioid use will be used at baseline and at the 4-month follow-up. It employs a 5-point Likert scale from 0 (no symptoms) to 5 (severe symptoms) where higher points indicate more symptoms. The following symptoms will be monitored: difficulties to concentrate, mood disturbance (anxiety or depression), constipation, diarrhea, nausea, vomiting, anorexia, dry mouth, fatigue or easily worn out, sleepy or fall asleep easily in daytime, dizziness, headache, flushing, sweating, and itching. Other bothersome symptoms can also be reported by the participant. This scoring is used in the trial in the clinical evaluation of tapering effects experienced by the participants.

##### Global opinion about tapering

At follow-up, all participants are asked: How do you consider your life situation has been affected by tapering opioids? Possible answers are (1) improved, (2) no change, and (3) impaired.

##### Opioid replacement therapy

Opioid replacement therapy is not registered in the SPDR as buprenorphine or methadone is dispensed at addiction care centers. Data is therefore derived from medical records at 12 months after the received intervention.

### Participant timeline {13}

Participants will be enrolled in the trial for 12 months (intervention) or 16 months (control) following baseline assessment. The structured tapering intervention has a 4-month duration, but may be prolonged.

Participants denying tapering, but accepting to participate, will be followed up after 12 months for dropout analysis (Fig. 1).

A SPIRIT diagram (Table 1) is provided detailing the timing of enrolment, interventions, and assessments. Any methodological changes in the study design or sample size that may potentially affect the participants’ safety or study procedures will be discussed in the committee of ethics.

**Table 1 Tab1:**
[figure not shown]
SPIRIT diagram

Schedule of enrolment, interventions, and assessments

### Sample size {14}

A “responder” to treatment is a participant who experiences at least a 50% reduction in opioid consumption [28]. Estimation of sample size was based on an effect size of 0.5 (Cohen’s *d*) 80% power, *α* = 0.05, and drop-off at 10%. The results from the calculation indicated the need for 70 individuals in each group.

### Recruitment {15}

To reach the sample size, additional sites at pain clinics in other parts in Sweden were invited during 2020/2021.

## Assignment of interventions: allocation

### Sequence generation {16a}

The allocation sequence is generated by computer to intervention or control in ratio 1:1 and is thereafter kept in sealed envelopes prepared by independent staff for an allocated group of 140 participants. Sealed envelopes will be kept in Lund and allocation will consequently take place in Lund.

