## Administrative information

**Table Taba:** 

Title	Tapering of prescribed opioids in patients with long-term non-malignant pain (TOPIO) – Efficacy and effects on pain, pain cognitions, and quality of life: a study protocol for a randomized controlled clinical trial with a twelve-month follow-up	
Trial registration {2a and 2b}.	Registered in Clinicaltrials.gov with id: NCT03485430, “Tapering of Long-term Opioid Therapy in Chronic Pain Population. RCT with 12 Months Follow up (TOPIO)”. First release date: 26/03/2018, retrospectively registered. First patient in trial 22/03/2018. https://clinicaltrials.gov/ct2/show/NCT03485430.	
Protocol version {3}	Record log in Clinical Trials:	
	06/22/2021	Author’s comment: Collaborating Centers in Gothenburg and Linkoeping are added as intervention expands to a multi-center trial. These centers will be recruiting participants and performing intervention with start autumn 2021. As no inpatient tapering has been performed since trial start this way of conducting intervention is no longer permitted.
	09/01/2020	Author’s comment: Acronym added to title. Exclusion criteria more thoroughly described but has been the same since start in March 2018. The trial has only recruited patients with prescribed opioids and not recruited participants with illicit drug use.
	05/07/2020 09:16 ClinicalTrials.gov	PRS Review comments recorded. Listed each Outcome Measure separately, using “Add a __ Outcome Measure” feature, please use/keep this format for future records. ClinicalTrials.gov QA9
	05/06/2020 05:54	New power-calculation has been performed January 2020. Study period is prolonged due to this. Outcome measurements has been more thoroughly described in this last entry. Data-collection has been the same since start in March 2018.
	03/30/2018 14:18 ClinicalTrials.gov	Made minor editorial changes (e.g., spelling, grammar, punctuation). ClinicalTrials.gov QA37
Funding {4}c	Lund University Hospital, Lund University, Southern Healthcare Region and Greta and Johan Kock’s Foundation.	

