
Follow-up will be performed by a nurse, preferably by phone, but can be made possible in person. Visits are necessary if multi-dose drug dispensing proves necessary. The number of contacts with the nurse is optional and decided by the participant in cooperation with the nurse. During tapering, the nurse may slow down tapering if participants are having problems following the plan or report a considerable decline in health and function.

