## Trial status

The first participant was recruited in March 2018. To date, 62 patients are allocated to the intervention or control group. At this rate, the allocation process is assumed to proceed until 2024 to reach the goal of 140 randomized participants. With additional trial sites being added in 2021 and 2022, the recruiting process may end earlier. During the 2025 follow-up, data processing and manuscript preparation are planned.

The current version of the protocol: Clinical Trials.gov PRS 06/22/2021 by [name], not yet publicly released.

Due to the COVID-19 pandemic, the recruitment process was brought to a halt in March 2020 and resumed on 1 September 2020 without any changes of the study population, but with an option for participants to take part in follow-up after intervention fully by phone or video. During January 2021, a halt in recruitment again took place for 1 month. Due to the COVID-19 pandemic, follow-up visits have been performed mostly by phone. Elderly, beyond the age of 70, was not allowed to enter into the trial between 7 January and 7 June 2021.

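### One 1:1 list for all 140 participants, without site strata or a site term at 4 months, does not assure balance within the two late-joining sites; the effect is small and the remedy cheap

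*Protocol article*

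**What the plan says.** Sequence generation {16a} specifies a computer-generated 1:1 sequence kept in "sealed envelopes prepared by independent staff for an allocated group of 140 participants". The envelopes stay in Lund and allocation takes place there. The figure of 140 is the target for the whole trial. No blocks and no stratification by site are named.

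The trial began in March 2018 and was later enlarged. The record log under Administrative information, dated June 2021, says "Collaborating Centers in Gothenburg and Linkoeping are added as intervention expands to a multi-center trial", with recruitment there from autumn 2021. Study setting {9} lists three sites. Trial status reports: "To date, 62 patients are allocated to the intervention or control group".

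Statistical methods {20a} compares the arms at 4 months with a paired t-test for the primary outcome and a Wilcoxon signed-rank test for the secondary outcomes. Neither contains a term for site.

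Sample size {14} states: "Estimation of sample size was based on an effect size of 0.5" (Cohen's d), with "80% power, *α* = 0.05" "and drop-off at 10" per cent; the result "indicated the need for 70 individuals in each group".

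**The concern.** A single 1:1 list can balance the arms over 140 participants, but it does nothing to balance them within a clinic that contributes perhaps 20 of them. The three clinics may differ in the patients referred to them. Controls return to usual care for 4 months, and usual care may also differ by place. If a new site happens to send more of its participants to one arm, part of its difference from the other sites enters the crude arm comparison. The named tests have no site term to remove it.

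At stake are a little precision and some chance confounding by case mix and usual care. Site can still be adjusted for in the analysis after recruitment, but balance within a site can be arranged only before its participants are allocated.

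**Working it through.** **The plan's own figure.** Inputs from Sample size {14}: d = 0.5, power 80%, alpha 0.05 (two-sided assumed, since sidedness is not stated), drop-off 10%.

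- n per arm = 2 × (1.960 + 0.842)² / 0.5² = 62.8, so 63.
- Allowing for drop-off: 63 / 0.90 = 70. This reproduces the stated 70 per group. A one-sided test would give 50, then 56, which does not match.
- Power at 63 evaluable per arm is 80.1%.

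**Participants still to be allocated.** 140 − 62 = 78. The number expected per new site is not given, so it is varied as an assumption. An equal share over three sites would be 78 / 3 = 26.

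**Chance of a 40:60 split or worse at one new site.** Whether the list is blocked or otherwise restricted is not stated, so three models are shown:

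| Participants at site | Remaining 78 exactly 39:39, drawn at random | Whole list 70:70 | Simple randomisation |
|---|---|---|---|
| 20 | 43.7% | 46.9% | 50.3% |
| 30 | 24.4% | 30.3% | 36.2% |

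The first two columns are hypergeometric and the third is binomial with probability 0.5. With 26 participants, the second and third models give 28% and 33%. Under the 70:70 model, the chance that at least one of two new sites splits this unevenly is 72% with 20 participants each and 47% with 26 each.

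**Effect on precision.** A 40:60 split keeps 4 × 0.4 × 0.6 = 96% of the information that an equal split of the same site would give. Simulating the 70:70 list over three sites with a site-adjusted comparison, the mean loss of efficiency is about 1.4%, with about 4.5% lost at the 5th percentile. Power is then 79.6% on average and about 78.4% in a poor draw, against 80.1%.

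**Effect on the crude estimate.** If one site's mean outcome differs from the rest by δ SD, and its arms differ by k participants, the crude arm difference shifts by δ × k / 70. Take δ = 0.5 (assumed) and a site of 20:

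- Typical draw, 8:12, k = 4: 0.5 × 4 / 70 = 0.03 SD.
- Poor draw, 6:14, k = 8: 0.5 × 8 / 70 = 0.06 SD.

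Under the 70:70 model the SD of k at such a site is 4.2, so these are draws of about one and two SDs. The planned effect is 0.5 SD, and the standard error of the arm difference at 63 per arm is √(2/63) = 0.18 SD.

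**The case against.** The strongest case against raising this has three parts.

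First, the article is condensed. Blocks, strata and a site covariate may stand in the full protocol or analysis plan. This holds for blocking, which the article leaves open, and it limits how firmly the point can be put. It does not remove the point, because the article does fix a mechanism: one sequence for one group of 140, allocated from Lund. Separate lists per site would be described differently.

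Second, randomisation without site strata is legitimate and unbiased, and its chance imbalance is already part of the standard error. This stands in full. The split probabilities sound large, but a 40:60 split in one small site does little harm.

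Third, small blocks per site make allocation easier to guess in an open trial. That cost is real, though varying and undisclosed block sizes limit it.

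Four stronger readings are tempting and are not supported:

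- **The list was prepared for Lund alone.** The text says only that envelopes for 140 participants are kept in Lund; 140 is the whole-trial target.
- **The arms are unbalanced within sites.** Balance is not assured, which is a weaker statement.
- **Staff discretion over the taper confounds the arms.** The article does say "the nurse may slow down tapering if participants are having problems following the plan or report a considerable decline in health and function", but up to 4 months this acts only in the tapering arm. Variation in delivery between clinics is a difference in treatment effect, which stratified allocation would not remove.
- **Per-site lists would allow the effect to be checked at each clinic.** The Discussion speaks of easing dissemination, not of estimating site-specific effects. A site of 20 to 30 participants could not support such an estimate even at exactly 1:1.

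**Conclusion.** The point holds as a cheap improvement and not as an error. As described, neither the allocation nor the 4-month comparison takes account of site, although two sites join with 78 of 140 allocations outstanding. An uneven split of 40:60 or worse in a new site of 20 has close to even odds. The consequence is small: about 0.5 percentage points of power on average and under 2 points in a poor draw, and a possible crude shift of about 0.03 to 0.06 SD. The stated sample size reproduces and need not change.

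These sizes rest on assumed site numbers, on an assumed site difference of 0.5 SD, and on the list having no unreported strata. If the full protocol already stratifies by site, the allocation part of the point falls away. If the analysis plan already includes site, the analysis part does.

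**What to change.** Before the new sites start:

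- Keep the 62 existing allocations as they are (and any made since).
- Have the independent staff replace the unused envelopes with separate 1:1 lists for Lund, Gothenburg and Linköping, in block sizes that vary at random and are not disclosed to those who recruit. Allocation can still run from Lund.
- Include site as a factor in the between-group comparison at 4 months. The named tests have no place for it, so this calls for a regression-type model of the arm difference.
- State the stratification in Sequence generation {16a} and the site factor in Statistical methods {20a}.

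The cost is one new computer-generated list and envelope set, plus a protocol amendment. It needs no additional participants or visits. The downside is slightly more predictable allocation in an open trial. If the lists cannot be replaced in time, the site factor alone removes the chance confounding by average differences between sites, at the small loss of precision shown above.
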